**Fig. 1 Fig1:**
[figure not shown]
Method for calculating the prevalence of HIV viraemia among diagnosed and undiagnosed gay and bisexual men

#### Outcome 2

HIV incidence will be calculated using repeat testing among the negative cohort, [18] which will consider patients with two or more HIV tests for whom the first test was negative. We expect that more than 80% of gay and bisexual men will have at least two tests over the study period. An incident infection will be defined as an HIV diagnosis following a negative test and time at risk will be calculated as the time between each patient’s first and last test or a patient’s first test and HIV diagnosis. The number of incident infections will be divided by the person time (in years) at risk.

#### Outcome 3

Data from the positive cohort will also be used to calculate the incidence of ART initiation (i.e., the point at which ART is initiated) with the follow-up period defined as the time after HIV diagnosis (person years of infection). This variable will be restricted only to men diagnosed with HIV during the study period.

#### Outcome 4

Data from the negative cohort will be used to calculate the incidence of repeat diagnostic HIV testing. The incident event is defined as the point at which a patient achieves a second HIV test within six weeks to 12 months of a previous test, with follow-up time defined as the period between a patient’s first HIV test and last clinical encounter. Follow-up time will cease if a patient has no recorded service event of any kind within a two year period but will resume at the point of future service events (i.e., reengages with a participating service). Follow-up will also cease if a patient is diagnosed with HIV.

#### Outcome 5

Among the positive cohort, the incidence of viral suppression will be calculated. Viral suppression is defined as two consecutive viral load tests of <200 RNA copies/mm^3^ separated by at least three months; the first test will be taken as the point of suppression for calculating time. This variable will only be calculated among patients with no history of previous treatment and will exclude those for whom there is no or only one viral load test result. We will conduct a sensitivity analysis with a higher viral load threshold of <1000 RNA copies/mm^3^.

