**Methods:**

Over the period 2009 to 2017, we will establish two cohorts making use of clinical and laboratory data electronically extracted retrospectively and prospectively from 73 health services and laboratories in the states of New South Wales and Victoria. The ‘positive cohort’ will consist of approximately 13,000 gay and bisexual men (>90% of all people living with HIV). The ‘negative cohort’ will consist of at least 40,000 HIV-negative gay and bisexual men (approximately half of the total population). Within the negative cohort we will use standard repeat-testing methods to calculate annual HIV incidence. Community prevalence of viraemia will be defined as the proportion of men with a viral load ≥200RNA copies/mm^3^, which will combine viral load data from the positive cohort and viraemia estimates among those with an undiagnosed HIV infection. Using regression analyses and adjusting for behavioural and demographic factors associated with infection, we will assess the temporal association between the community prevalence of viraemia and the incidence of HIV infection. Further analyses will make use of these cohorts to assess incidence and predictors of treatment initiation, repeat HIV testing, and viral suppression.

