### Participants

Using de-identified data extracted from ACCESS sites, two patient cohorts of gay and bisexual men will be established: one comprising HIV positive men (‘positive cohort’) and the other HIV negative men (‘negative cohort’). The positive cohort will consist of approximately 13,000 HIV positive gay and bisexual men (approximately 90% of all gay and bisexual men with HIV in both states) and the negative cohort will consist of at least 40,000 HIV negative gay and bisexual men (approximately half of the population).

Both cohorts will be limited to men aged 16 years and older for whom there is at least once record indicating a history of sexual contact with other men. Indicators of same sex contact can be behavioural (i.e., self-reporting same sex partners), identity-based (i.e., recorded sexual orientation as gay or bisexual), or procedural (i.e., collection of an anal swab for STI testing). The positive cohort will include patients recorded as HIV positive or those who receive an HIV diagnosis during the study period. The negative cohort will include patients whose first record of HIV testing during the study period is negative. If during the course of the study a person is diagnosed with HIV, they will be reclassified to the positive cohort. Follow-up during the study period will be based on records from the participating services as well as the pathology conducted by participating laboratories.

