### Data analyses

TAIPAN will undertake four separate analyses to address the study aims (Table 2).

TAIPAN’s primary aim will be addressed by examining the temporal relationship between community prevalence of viraemia and incidence of HIV infection in gay and bisexual men. For each year of follow up, the community prevalence of HIV viraemia as determined by the calendar year will be entered as an independent variable in the regression. In addition to estimating the effect of community prevalence of viraemia, we will control at the individual level for other demographic, clinical and behavioural determinants of acquisition of new HIV infection, and recent sexual risk practices. We will use random effects Poisson models to undertake multi-level analyses that will allow us to include group-related variables (community prevalence of viraemia), individual variables (demographic, clinical, and behavioural) and time.

The study period will be divided into three-year periods defined by treatment guidelines and policy. The first period will encompass 2009–2011 and serve as a ‘before’ treatment as prevention period. The second period will encompass 2012–2014 and represent a transition period given that several Australian jurisdictions began to expand treatment as prevention initiatives during this time. And the third period will encompass 2015–2017, representing the full implementation of treatment as prevention given that early ART initiation was recommended for both individual and public health purposes. In regards to time lags, we assume that HIV incidence is affected by the estimated prevalence of virological suppression from the preceding year.

The second analysis will examine the temporal relationship between the three time periods described above and the incidence of treatment initiation among men newly diagnosed with HIV (Secondary Aim 1). Using the study periods described above in a regression analysis, incidence of treatment initiation among men newly diagnosed with HIV will be the outcome variable while controlling for clinical, demographic and behavioural factors. Given its historical role in determining when to initiate treatment, CD4 cell count at diagnosis and HIV viral load will also be included in the multivariate model.

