There have been only a few community-level studies of treatment as prevention in gay and bisexual men [27–30]. A consistent limitation in all these studies is the indirect measurement of HIV incidence, calculated either via mathematical modelling or derived from case notifications. Although case notifications in a highly tested population may be close to reflecting incidence, in Australia nearly a quarter of diagnoses are considered ‘late’ (CD4 cell counts of <350/mm^3^) [6] and trends in notifications can be influenced by fluctuations in diagnostic testing. One large, community-level study of heterosexuals in Africa measured HIV incidence directly between 2009–2012 and demonstrated a strong correlation between treatment coverage and HIV incidence at a community-level [31]. These findings, however, cannot be applied to gay and bisexual men due to population differences in sexual behaviour and HIV incidence. In addition, the levels of HIV testing and treatment coverage reported in this study were of the levels achieved in Australia more than a decade ago. Furthermore, any community-level evaluation of treatment as prevention must account for potential confounders, including other prevention and risk reduction strategies and notably the uptake of PrEP.

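### Dating infection at diagnosis while cutting negative men's risk time at their last test pushes incidence down in 2009 and up in 2017, so a real decline can disappear

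*Protocol article*

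**What the plan says.** All references are to the protocol article.

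- **Event (Study outcomes, Outcome 2):** "An incident infection will be defined as an HIV diagnosis following a negative test and time at risk will be calculated as the time".
- **Risk time:** the same sentence then fixes the interval, which is the one "between each patient’s first and last test or a patient’s first test and HIV diagnosis". The rate is a simple quotient: "The number of incident infections will be divided by the person time (in years) at risk".
- **Who is counted:** Outcome 2 takes "patients with two or more HIV tests for whom the first test was negative". Entry is tied to the study window (Participants): "The negative cohort will include patients whose first record of HIV testing during the study period is negative".
- **Calendar use:** the Abstract says "we will use standard repeat-testing methods to calculate annual HIV incidence". Data analyses relates incidence to calendar-year viraemia, defines the periods 2009–2011, 2012–2014 and 2015–2017, and adds a lag: "we assume that HIV incidence is affected by the estimated prevalence of virological suppression from the preceding year".
- **Sensitivity:** alternative viral-load thresholds are planned for Outcomes 1 and 5. Nothing is planned for the date of infection.

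**The concern.** A seroconverter was infected somewhere between his last negative test and his diagnosis. Placing the event at the later end moves infections into later calendar years than the ones in which they arose. Two edge effects follow.

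- **Start of window.** Every man enters with a negative test, so person-time accrues at once. No event can be recorded until his next test. The first year is too low.
- **End of window.** A man who stays negative contributes nothing after his last test, while every diagnosis up to 31 December 2017 is counted with its full risk time. The last year is too high.

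Starting risk time at the first test is correct in itself. The fault is dating the event at diagnosis while negative men are censored at their last test.

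The primary question is whether incidence falls after viraemia falls. This rule builds in an upward trend at exactly the two ends being compared, and adjustment for individual covariates does not change an event date. The size of the trend depends on test spacing, and testing is itself being scaled up. The Discussion faults earlier studies because "trends in notifications can be influenced by fluctuations in diagnostic testing", yet this outcome is also sensitive to test timing. The delay to diagnosis also adds an unstated shift to the assumed one-year lag.

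**Working it through.** **The plan's own figure first (Sample size).** Incident cases: 0.80 × 420 = 336 per year. Events needed for a hazard ratio of 0.80 at two-sided 0.05 and 80% power: 4 × (1.96 + 0.84)² / (ln 0.80)² ≈ 631. Two adjacent years with 336 and 0.80 × 336 = 269 events give 78.3% power; 336 + 336 gives 82.4%. The stated 80% is reproduced, but it presumes unbiased annual rates.

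**Inputs**

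- Window 2009–2017, entry at first negative test, at least 40,000 men (Study design, Participants).
- Test frequency: 80% tested yearly and 25% of those once more (Sample size), so 0.80 × 1.25 = 1.0 test per man-year, a mean gap of about one year.
- True decline: 30%, to 420 per year (Sample size), so 420 / 0.70 = 600 before.
- Assumed: starting incidence 0.80 × 600 / 40,000 = 1.2 per 100 person-years (PY), and test gaps either regular (0.5 to 1.5 times the mean) or random (exponential).

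**End years by hand (flat 1.2 per 100 PY, regular one-year gaps, first tests spread evenly over 2009)**

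- *2009.* For a first test at time u and next gap g, a diagnosis falls in 2009 only if u + g < 1. Expected events per man: 0.012 × ∫ g(1 − g) dg over 0.5 to 1 = 0.012 × 1/12 = 0.0010. Person-years per man: 0.5. Rate: 0.0010 / 0.5 = **0.20 per 100 PY**.
- *2017.* Events per man: about 0.012. With B the time from last test to the end of the year, P(B > x) = 1 − x up to 0.5 and (1.5 − x)²/2 from 0.5 to 1. The mean time lost within 2017 is 0.375 + 0.146 = 0.521 years, leaving 0.479. Rate: 0.012 / 0.479 = **2.5 per 100 PY**.

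**Simulation of the Outcome 2 rule, flat truth of 1.2 per 100 PY, closed cohort, mean gap one year**

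| Gaps | 2009 | 2010 | 2011 | 2012 | 2013 | 2014 | 2015 | 2016 | 2017 | Ratio 2015–17 vs 2009–11 (truth 1.0) |
|---|---|---|---|---|---|---|---|---|---|---|
| Regular | 0.20 | 1.03 | 1.22 | 1.20 | 1.21 | 1.19 | 1.21 | 1.21 | 2.49 | 1.55 |
| Random | 0.32 | 0.68 | 0.90 | 1.07 | 1.13 | 1.21 | 1.29 | 1.54 | 3.24 | 2.43 |

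The regular row matches the hand calculation at both ends.

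**True 30% decline (ratio about 0.70).** Ranges are over separate simulations with closed or staggered entry. The last two columns come from 300 simulated studies of 40,000 men per row.

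| Mean gap, pattern | Ratio under the plan's rule | Significant decline | Significant increase |
|---|---|---|---|
| 6 months, regular | 0.85–0.89 | 90% | 0% |
| 6 months, random | 1.00–1.07 | 0% | 31% |
| 1 year, regular | 1.08–1.14 | 0% | 68% |
| 1 year, random | 1.6–1.8 | 0% | 100% |

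With infection placed at a random point between last negative test and diagnosis, and risk time ended there, the ratios are 0.68–0.73. A significant decline was found in all 300 studies in each of the four settings. With flat truth the same method gives 0.98–1.03.

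**Robustness, mean gap one year**

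- If 30–50% of infections are diagnosed within three months through symptoms, the plan's rule still gives 0.99–1.05 (regular) or 1.36–1.50 (random).
- Dropping both 2009 and 2017 gives 0.78 (regular) but 1.29 (random).

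**Hidden lag.** Mean time from infection to diagnosis is 0.27 years with regular six-monthly gaps and 0.54 years with regular yearly gaps. This comes on top of the stated one-year lag.

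**The case against.** The case for the plan is mostly about size and scope.

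1. **Random gaps are the harsher assumption, and the document does not support them.** With regular gaps the error sits mainly in 2009 and 2017, and the years between are close to the truth. With regular six-monthly testing the decline shrinks but survives. This stands, and it is why the claim is that a decline can disappear, not that it must. But at the article's own frequency of about one test per man-year, even regular gaps turn 0.70 into about 1.1.
2. **The period ratio is not the primary estimator.** The primary model regresses incidence on lagged viraemia. No 2008 viral-load data are described, so 2009 may have no lagged exposure and drop out. This is fair, and the effect on the viraemia coefficient was not estimated. Dropping 2009 still leaves a ratio of 0.92–1.48 at one-year gaps, and 2017 stays in.
3. **The outcome is not a notification count.** It has a person-time denominator and requires a prior negative test. True, but its trend still depends on when men test.
4. **The article condenses a longer document.** It calls the method standard and cites a reference. Allocation to calendar year is written out only for repeat testing, so placing HIV events in the year of diagnosis is an inference. It is the natural one: Outcome 2 states the event and the end of risk time explicitly, and nothing shown overrides it.
5. **A midpoint might do as well as a random point.** On the period ratio with regular one-year gaps it does (0.71). With random one-year gaps and a flat 1.2 it still gives 0.83 in 2009 and 0.88 in 2017, so the end years stay distorted.

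**Conclusion.** The rule is wrong as written and must be fixed before annual incidence is related to viraemia. Its direction follows from the definitions alone: low at the start of the window and high at the end, against the study hypothesis. Its size rests on assumed test spacing, anchored on the roughly one test per man-year in the Sample size section. At that frequency a true 30% fall appears as a rise of about 10% with regular gaps, and of 60% to 80% with random gaps. With six-monthly testing the fall is attenuated to 11–15% (regular) or vanishes (random). Confidence is high on the mechanism and moderate on the exact size. The figures are for the period rate ratio, not the regression coefficient.

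**What to change.** In Outcome 2 and in the primary analysis:

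- For each seroconverter, draw the infection date uniformly between last negative test and diagnosis. Use multiple imputation with, for example, 100 or more draws, combined by Rubin's rules. An interval-censored likelihood is an acceptable alternative.
- End risk time at the drawn date, and allocate both event and person-time to calendar years, and so to lagged viraemia, on that basis. Men who stay negative are still censored at their last test.
- Keep the diagnosis-date version as a sensitivity analysis. Do not use a single midpoint, and do not rely on dropping the end years.
- State the calendar-year allocation explicitly, and say how 2009 is handled under the one-year lag.

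The cost is wording and programming, with slightly wider intervals. No new data are needed, because Outcome 2 already requires each man's test dates.

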### Study outcomes

Table 2 outlines the study aims, relevant cohorts, and study outcomes.

**Table 2 Tab2:** Overview of TAIPAN research aims, study cohorts involved and outcome indicators

	Cohort(s)	Outcome indicators
Primary aim		
Determine the relationship between viraemia and incidence of new HIV infections among gay and bisexual men	Negative Positive	• HIV incidence • Viraemia prevalence
Secondary aims		
1. Assess the association between changes in guidelines and policies and earlier uptake of HIV treatment among gay and bisexual men	Positive	• Incidence of treatment initiation
2. Identify incidence and predictors of repeat HIV testing among HIV negative gay and bisexual men	Negative	• Incidence of repeat testing (second HIV test within a 12 month period)
3. Identify incidence and predictors of supressed HIV viral load among HIV positive gay and bisexual men	Positive	• Incidence of viral suppression

#### Outcome 1

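### Repeat-testing rate (Outcome 4): events can occur only six weeks to 12 months after a test, but person-time runs from first test to last clinical encounter, so numerator and denominator do not match

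*Protocol article*

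**What the plan says.** In the protocol article (Methods, Study outcomes, Outcome 4), the event is the point at which "a patient achieves a second HIV test within six weeks to 12 months of a previous test". The person-time is set in the same sentence, "with follow-up time defined as the period between a patient’s first HIV test and last clinical encounter". Two further rules follow. First, "Follow-up time will cease if a patient has no recorded service event of any kind within a two year period", with time resuming if the man re-engages. Second, "Follow-up will also cease if a patient is diagnosed with HIV".

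Entry is set under Participants: "The negative cohort will include patients whose first record of HIV testing during the study period is negative". No second visit is required.

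Under Data analyses, both the time and the events are allotted to calendar years, change over time is assessed, and a regression looks for predictors. Table 2 gives the outcome in short form: "Incidence of repeat testing (second HIV test within a 12 month period)".

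**The concern.** A rate is interpretable when its person-time is the time during which the event could have happened and would have been counted. Outcome 4 departs from this in two ways.

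- **Time that should count is left out.** A man whose first test is his only encounter has a follow-up of zero. He has failed to retest, yet he adds nothing to numerator or denominator.
- **Time that should not count is put in.** A man who keeps attending without testing goes on adding time after 12 months from his last test, when a further test would no longer qualify.

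A retest is itself an encounter, so the length of follow-up depends on the outcome. At stake is Secondary Aim 2: the annual rates, their trend, and comparisons between groups or services whose patients differ in how often they return or attend for other reasons.

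**Working it through.** **The plan's own figure.** Sample size gives 8000 repeat testers a year: 40,000 × 0.80 × 0.25 = 8000. This reproduces exactly. It is a head count that uses no person-time, so the point does not turn on it.

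**Inputs from the article.** Event window: six weeks to 12 months. Follow-up: first test to last encounter. Share with two tests: "We expect that more than 80% of gay and bisexual men will have at least two tests over the study period" (Outcome 2). At most about 20% would then have one test. Some of those may attend for other care, so 20% is an upper bound on the share never seen again.

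**Inputs assumed, not in the article.** Among men who return, 90% retest every 9 months for 3 years (4 events in 3 years each) and 10% attend for 1 year without retesting.

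**Step 1: effect of never-returners.** Take 1000 men, 20% never seen again: 200 never return, 720 retest, 80 attend only.

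- Events: 720 × 4 = 2880.
- Person-years as defined: 720 × 3 + 80 × 1 + 200 × 0 = 2240. Rate: 2880 / 2240 = 128.6 per 100 person-years.
- Crediting 1 year to each never-returner: 2880 / 2440 = 118.0. Ratio 128.6 / 118.0 = 1.09.
- Crediting 2 years: 2880 / 2640 = 109.1. Ratio 128.6 / 109.1 = 1.18.

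| Never-return share | As defined | 1 year credited | 2 years credited |
|---|---|---|---|
| 0% | 128.6 | 128.6 | 128.6 |
| 10% | 128.6 | 123.7 | 119.1 |
| 20% | 128.6 | 118.0 | 109.1 |
| 50% | 128.6 | 94.7 | 75.0 |

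The defined rate is the same in every row. If the share rose from 10% to 20% between two years, the credited rate would fall by about 5% (123.7 to 118.0) or 8% (119.1 to 109.1), and the defined rate would not move.

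**Step 2: men who attend without retesting.** With no never-returners, let the share attending for 1 year without a retest rise from 0% to 10%, 30% and 50%. The defined rate is 133.3, 128.6, 116.7 and 100.0 per 100 person-years. Failure to retest among men who keep attending is therefore registered.

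**Step 3: time in which no event is possible.** A man who retests at 18 months adds 1.5 person-years and no event, although a retest could have counted only in the first 12 months. Another man tests at 0 and 6 months, then attends to year 3 without testing. As defined: 1 / 3 = 33 per 100 person-years. With an interval opened at each test (six-week start ignored): 1 / (0.5 + 1.0) = 67. Here the plan's rate is too low.

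**Step 4: the two-year rule.** If it only handles gaps between encounters, single-visit men still add nothing. If it lets time run up to two years past the last encounter, single-visit men do add time, but that contradicts an end point at the last encounter and brings in time beyond 12 months after a test.

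**The case against.** Ending follow-up at last contact is a common choice in a cohort built from records, since nothing is known about a man after he leaves. Linkage across services means that not returning to one clinic need not end his follow-up. The negative cohort covers about half the population, and laboratories were chosen for confirmatory and viral load testing, so negative tests done elsewhere may be missed. Counting such men as not retested brings in a bias of its own. This part stands and shapes the fix. It does not rescue the present definition, because last contact here is not independent of the outcome.

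Four stronger readings are tempting, and the article does not support them.

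- A reader might infer that the rate cannot register any failure to retest. Step 2 shows otherwise; only non-return goes unseen.
- A reader might infer that the rate must be too high. Step 3 gives a case where it is too low, and the attendance mix is not stated.
- A reader might infer a several-fold error. Suppose only 50%, 30% or 10% of men return, each once, at 6 months. The defined rate is 200 per 100 person-years each time, against 40, 26 and 9.5 with an interval at every test. But non-return of 50% to 90% is far from the article's expectation that more than 80% will have two tests.
- A reader might take Table 2, which omits the six-week minimum, as a rival definition. The table is captioned as an overview, and its wording is shorthand.

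**Conclusion.** The concern holds in limited form. The stated denominator is not the time at risk for the stated event. It leaves out men lost after a single test and includes time when no event could count. These errors act in opposite directions, and the net bias in annual rates, trend and predictors cannot be derived from the article.

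The 9% to 18% inflation isolates the first error at the 20% upper bound. It rests on the assumed visit pattern and on crediting one or two years to each never-returner; it is not an estimate of the net error. The wording of the two-year rule is an ambiguity that must be settled, but neither reading makes the denominator match the event. This is a flaw in a rule that the article fixes, not detail left to an analysis plan. It affects a secondary aim and should be corrected before analysis.

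**What to change.** Open an at-risk interval at each negative test. Run it from six weeks after that test to the earliest of the next test, HIV diagnosis, 12 months or 31 December 2017, whether or not the man is seen again. Count at most one event per interval and use the summed interval time as the denominator, still allotted to calendar years. The two-year rule is then not needed for this outcome; if it is kept, state whether time accrues after the last encounter and reconcile it with the sentence before it.

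Report a sensitivity analysis that censors each interval at the last recorded encounter, and say that retests outside the network count as not retested in the main analysis.

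The cost is a revised definition and a little more programming on data already being extracted. Rates may move in either direction.

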The community prevalence of viraemia is defined as the proportion of gay and bisexual men (diagnosed and undiagnosed) with a viral load of ≥200 RNA copies/mm^3^. A viral load of ≥200 was selected as this is a commonly-used clinical marker of viral suppression and a recent meta-analysis found no transmission of HIV among individuals with less than 200 RNA copies/mm^3^ [14]. Community prevalence of viraemia was selected as it has been demonstrated to have the strongest correlation with HIV incidence over other measures (e.g., mean viral, treatment coverage) [15]. Our measure of viraemia will comprise the following four components:Annual prevalence of viraemia: will be calculated within the positive cohort using the annual prevalence of viral load test results of ≥200 RNA copies/mm^3^ (‘viraemia’) at each patients last viral load test within a calendar year. We will conduct sensitivity analyses to include any viral load test ≥200 RNA copies/mm^3^ in a year and also using a higher threshold of ≥1000 RNA copies/mm^3^.Annual prevalence of diagnosed HIV infection among gay and bisexual men: will be estimated using population prevalence techniques developed by and used for Australia’s national HIV surveillance [6]. This approach produces a prevalence estimate using data on HIV diagnoses from Australia’s National HIV Registry, adjusting for duplicate entries, deaths, and migration outside of Australia. For this estimate we will focus on HIV diagnoses where homosexual contact is identified as the route of transmission.Annual prevalence of undiagnosed HIV infection among gay and bisexual men: will be estimated using standard back-project models [16] and validated against a separate bio-behavioural survey conducted in 2013–2014 and to be repeated in 2017 [17].Prevalence of viraemia in gay and bisexual men with undiagnosed HIV infection: will be calculated using an estimate of undiagnosed infection obtained from the back-projection models coupled with the assumption that all undiagnosed men have viral loads of ≥200 RNA copies/mm^3^. We will also consider different viral load levels among undiagnosed men by using data from the National HIV Registry and stratifying viral load at diagnosis by HIV testing history (i.e., reported time since HIV test prior to diagnosis).

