The third analysis will determine incidence and predictors of repeat HIV testing (Secondary Aim 2). To calculate annual estimates we will allocate follow-up time and the incident of repeat testing (i.e., the point at which a second test is achieved) to the calendar year in which it occurs. With this approach it is possible that a patient might achieve multiple incidents of repeat testing in one calendar year. In addition to evaluating changes in the incidence of repeat HIV testing over time, this analysis will employ a regression analysis to identify demographic, behavioural and clinical factors associated with repeat testing incidence among gay and bisexual men in the negative cohort.

The fourth analysis will estimate the incidence of viral suppression among those newly diagnosed and predictors of incidence of viral suppression among the positive cohort (Secondary Aim 3). This analysis will employ Cox proportional hazards regression. Further, we will estimate the median time from diagnosis to first viral suppression by calendar year among those who are diagnosed during the study period, stratified by CD4 cell count at diagnosis. For this analysis and all others, statistical significance will be set at *p* < 0.05.

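### Outcome 5 makes both the viral suppression event and its risk set depend on how often a man is tested later

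*Protocol article*

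**What the plan says.** The rules are in the protocol article, Methods, Study outcomes, Outcome 5.

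- Event: "Viral suppression is defined as two consecutive viral load tests of <200 RNA copies/mm^3^ separated by at least three months".
- Event date: "the first test will be taken as the point of suppression for calculating time".
- Population: "This variable will only be calculated among patients with no history of previous treatment", and the variable "will exclude those for whom there is no or only one viral load test result".
- Sensitivity: "We will conduct a sensitivity analysis with a higher viral load threshold of <1000 RNA copies/mm^3". Neither the spacing nor the exclusion is varied.

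Under Data analyses, the fourth analysis covers incidence and predictors of suppression: "This analysis will employ Cox proportional hazards regression". It also reports the "median time from diagnosis to first viral suppression by calendar year" among men diagnosed during the study, stratified by CD4 count at diagnosis. Study design sets the end of the data at 31 December 2017. Data sources describes routine service records, and no viral load schedule is given anywhere.

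**The concern.** Two features of the definition look forward in time.

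First, whether a man will have two viral loads is not known at diagnosis, when his clock starts. Requiring two selects the risk set on later behaviour and later follow-up. Men who leave care after no test or one test are removed instead of censored. So are men who keep attending without viral loads, and men diagnosed so late in 2017 that two tests were not feasible. This last group is concentrated in one calendar year, and results are reported by calendar year.

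Second, the rule asks for adjacent low results with a gap of at least three months. A man tested more often than that may be continuously below 200 and still have no qualifying pair, or get one only when a gap happens to lengthen. Monitoring frequency then enters the event date. If it differs between services or changes over 2009 to 2017, it can appear as a predictor of suppression or as a time trend.

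At stake are the incidence, the hazard ratios and the median times for Secondary Aim 3.

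**Working it through.** The documents give no figure for the number of men excluded or for the gaps between tests, so there is none to reproduce. The power statement for this outcome (80% for HR = 1.15) uses neither rule and is not at issue here.

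**Exclusion: direction.** Let d_j be the number of events and n_j the number at risk at event time j. Every event requires two results, so every man with an event passes the two-test filter. The exclusion leaves each d_j unchanged and can only reduce n_j. Each hazard d_j/n_j is therefore the same or larger. The Kaplan-Meier share suppressed is the same or higher, and the median time is the same or shorter, than if the men were kept and censored. For hazard ratios the direction is not determined.

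**Exclusion: size.** A man censored before the first event time is in no n_j, so restoring him changes nothing in a Kaplan-Meier or Cox estimate. What matters is how long the excluded men are observed. For an incidence rate, assume (none of this is in the documents) that 10% of men are excluded and that the other 90% contribute 6 months each:

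- Person-time with the exclusion: 0.90 × 6 = 5.4 months per man.
- Excluded men observed for 1 month: 5.4 + 0.10 × 1 = 5.5. The rate is multiplied by 5.4/5.5 = 0.982, a fall of about 2%.
- Excluded men observed for 12 months without viral loads: 5.4 + 0.10 × 12 = 6.6. The rate is multiplied by 5.4/6.6 = 0.818, a fall of about 18%.

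The result depends on follow-up that the documents do not describe.

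**End of data.** A low result after 30 September 2017 cannot be followed by another at least three months later before 31 December 2017. Men with two or more tests still contribute time in that quarter although no event can start in it. This lowers the latest incidence, while the exclusion raises it.

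**Spacing: worked schedules.** All results listed are below 200, in months from diagnosis. The proposed rule takes the first low result that is followed by another at least three months later with no high result between.

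| Low results at months | Gaps | Literal rule | Proposed rule |
|---|---|---|---|
| 2, 4, 6, 8, 10, 12 | all 2 | no event | 2 (confirmed at 6) |
| 2, 4, 6, 9 | 2, 2, 3 | 6 | 2 (confirmed at 6) |
| 3, 6, 9 | 3, 3 | 3 | 3 |
| 2, 8 | 6 | 2 | 2 |

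In the second row the event is dated 6 − 2 = 4 months late.

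**Spacing: simulation.** Men are below 200 from their first low test and followed for 2 years. Gaps are gamma-distributed with coefficient of variation (CV) 0.1, 0.25 or 0.5. The gaps are assumptions.

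| Mean gap | Share counted, literal rule (CV 0.1 / 0.25 / 0.5) | Mean delay among those counted |
|---|---|---|
| 2 months | 0% / 32% / 88% | 8.9 and 6.2 months (CV 0.25, 0.5) |
| 2.5 months | 23% / 88% / 98% | 9.4 / 6.1 / 4.1 months |
| 3 months | 99.4% / 99.5% / 99.8% | 2.8 / 2.7 / 2.5 months |
| 4 months | about 100% | at most 1.1 months |
| 6 months | about 100% | at most 0.4 months |

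If the rule instead means all results low over a span of at least three months, 100% are counted with no delay in every one of these 2-year scenarios.

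**The case against.** The strongest reply is that Cox regression already deals with incomplete follow-up, and that men lost very early carry almost no information. Both parts are right. A reader might infer that everyone lost from care disappears. The documents do not support that: men lost after two or more results stay in and can be censored. A reader might also scale a 12-month proportion down by the excluded share. That treats excluded men as followed for the whole period and known to be unsuppressed. Censoring at last contact does not do so, and the plan reports no such proportion. Men with no or one linked result may also have had tests that were not captured or not linked, since Cohorts targets 95% or more of viral load tests and the linkage is probabilistic.

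A reader might likewise infer that frequently tested men are never counted. That holds only if every gap between low results stays under three months. One longer gap is enough to produce an event, though a late one. The authors may also have meant suppression sustained over at least three months, and an article may leave programming detail to a fuller document. But the text as printed supports the literal reading, and the two readings give different dates.

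Finally, thresholds are printed per mm³, as in "with a viral load of ≥200 RNA copies/mm^3". Since 1 mL is 1,000 mm³, a reader might infer a cut-off of 200,000 per mL. Study outcomes calls 200 a commonly used clinical marker, the label is consistent throughout, and nothing suggests that results would be converted. This is a label slip to correct and biases no outcome.

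What stands is the explicit selection on later tests. Outcomes 3 and 4 impose no comparable minimum number of results, so the design does not need it. The dependence of the event on test spacing also stands.

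**Conclusion.** The concern holds in limited form, for Secondary Aim 3 only. The primary viraemia measure uses each man's last viral load in the year and is not touched by these rules.

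The exclusion gives the same or higher incidence and the same or shorter median time than retaining and censoring the men would. This assumes that the target is all eligible newly diagnosed men and that the median is estimated with censoring. The effect is small if the excluded men leave at once and larger if they stay under observation without viral loads. The documents do not say which, so no single figure can be attached, and the rates worked above are illustrations only.

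The literal spacing rule has little effect where gaps are four months or more. It dates events late by roughly 2.5 to 2.8 months on average at a three-month mean gap, and it can miss many men at shorter gaps, all under assumed gap distributions. The planned threshold analysis would reveal neither problem.

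**What to change.** In Outcome 5:

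1. Keep every eligible newly diagnosed, previously untreated man at risk from diagnosis, censored at last contact whatever his number of viral loads.
2. Define the event as the first result below 200 that is followed by another below 200 at least three months later, with no result of 200 or more between them. Keep the date of the first.
3. End time at risk three months before data close, using the remaining tests only for confirmation. This gives each counted result the minimum window. Confirmation still depends on a test being done, which should be stated as a limitation.
4. Report the restriction to men with two or more results as a sensitivity analysis, beside the planned threshold analysis.
5. Print all viral load thresholds in copies/mL.

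The cost is new wording and minor reprogramming on data already to be extracted. Reported incidence may be slightly lower once the excluded men are kept. The revised event rule works in the other direction, so the net change is not known in advance.
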